# Eye movement desensitization and reprocessing (EMDR) therapy or supportive counseling prior to exposure therapy in patients with panic disorder: study protocol for a multicenter randomized controlled trial (IMPROVE)

**DOI:** 10.1186/s12888-022-04320-4

**Published:** 2023-03-14

**Keywords:** Exposure Therapy, Eye Movement Desensitization and Reprocessing (EMDR) therapy, Supportive Counseling, Randomized Controlled Trial, Anxiety Disorder, Panic Disorder, Cognitive-Behavioral Therapy (CBT)

## Abstract

**Background:**

Exposure-based therapy is the treatment of choice for anxiety disorders, but many patients do not benefit sufficiently from it. Distressing images of threat related to the future or past may maintain the anxiety symptomatology or impede exposure therapy. An intervention that targets threat-related imagery is eye movement desensitization and reprocessing (EMDR) therapy. The main goal of this multicenter randomized controlled trial is to investigate whether EMDR therapy plus exposure therapy, relative to supportive counseling plus exposure therapy, improves treatment efficacy, tolerability, and adherence in patients with panic disorder. In addition, we will examine potential predictors of optimal treatment allocation, mechanisms of change as well as the long term effects of treatment. Finally, we will assess cost-effectiveness.

**Methods:**

A multicenter randomized controlled trial mixed design will be conducted. Participants will be 50 patients, aged ≥ 18, diagnosed with a panic disorder. They will be randomly assigned to one of two conditions: EMDR therapy (i.e., flashforward strategy) or supportive counseling (each consisting of four weekly sessions of 90 min each) prior to exposure therapy (consisting of eight weekly sessions of 90 min each). Assessments will be made pre-treatment (T1), between-treatments (T2), post-treatment (T3), one month post-treatment (FU1) and six months post-treatment (FU2) by an assessor blind to treatment condition. The primary outcome measure is severity of panic-related symptoms. Secondary outcome measures are: tolerability of exposure therapy (initial avoidance, willingness to start exposure therapy, considered drop-out; no-show and drop-out), related symptomatology (generalized anxiety, depression), and functional impairment.

**Discussion:**

The primary goals of this research are to compare the efficacy, tolerability, and adherence of EMDR therapy plus exposure therapy and supportive counseling plus exposure therapy and to identify predictors, moderators, and mediators for treatment success. This multi-center research aims to make a significant contribution to our understanding as to how treatment for patients with anxiety disorders can be optimized, and elucidate who can benefit most from this novel approach.

**Trial registration:**

ISRCTN—ISRCTN29668369: Improving anxiety treatment by modifying emotional memories before real-life exposure. Registered 27 June 2022—retrospectively registered. ISRCTN—ISRCTN29668369.

## Background

Anxiety disorders are among the most common mental disorders, with about one out of 14 people meeting diagnostic criteria at any point of time [1]. These disorders comprise panic disorder, agoraphobia, social anxiety disorder, specific phobia, and generalized anxiety disorder. Their key elements are excessive fear in anticipation or the presence of the feared (innocuous) stimulus/stimuli and avoidance of disorder-related situations [2], which cause personal suffering and/or functional impairment [3]. Annual societal costs associated with anxiety-related disorders are estimated at about €74 billion in the European Union [4] and $42 billion in the United States [5].

Cognitive-behavioral therapy (CBT) is the psychological treatment of choice for anxiety disorders recommended in clinical guidelines [e.g., [6]], and it typically includes a combination of cognitive restructuring and behavioral (e.g., exposure) interventions [6, 7]. During exposure therapy, patients are systematically confronted with stimuli and situations associated with their anxiety disorder (e.g., bodily sensations in case of panic disorder), so that the patient learns that the anticipated feared outcome does not occur (e.g., having a heart attack) [8]. Meta-analyses have shown large effect sizes for CBT in anxiety disorders, especially when exposure strategies are used [9, 10].

A recent meta-analysis, however, shows that exposure-based CBT is moderately efficacious for anxiety disorders compared to other interventions when controlling for non-specific treatment or placebo (pill or psychological) effects [9]. There is substantial room for improvement for at least four reasons. First, about 25–30% of patients refuse to start exposure therapy, because they find it too aversive [11, 12]. Second, about 10–20% of patients drop out prematurely [12–14]. Third, although meta-analyses show substantial effect sizes for (exposure-based) CBT, the response rate (i.e., the percentage of patients showing significant clinical improvement) is around 50% [15]. Finally, little research has focused on relapse after (exposure-based) CBT [16–18], but recent findings suggest that it occurs in about 14% of cases [17]. Additionally, laboratory research has shown that even when exposure-based training is initially successful, learned fear can later return [19]. Taken together, these results underline the need for treatment optimization.

According to prevailing associative learning theories [20], the intensity of learned fear is determined by two factors: the strength of threat expectancy (e.g., expecting that dizziness or heart palpitations are harbingers of having a heart attack) and the mental representation of threat intensity (e.g., having a heart attack). Presumably, exposure therapy focuses specifically on the first factor: maximizing violations of threat expectancy [8]. It is not directly aimed at the second factor: the threat intensity representation [21] such as vivid and upsetting mental imagery of having a heart attack in a supermarket. Such imagery shares similarities with traumatic memories in posttraumatic stress disorder (PTSD) [21, 22]. Indeed, previous research showed that anxiety patients often report vivid and distressing mental images of threat [23, 24], related to past aversive events (“flash-backs”) or, likely more importantly, anticipated future threat (i.e., “flash-forwards”) [25, 26].

If patients with anxiety disorders experience intense threat imagery, they might be too anxious [27, 28] or unwilling to confront feared stimuli [28–30], which could explain the low attrition rates in exposure therapy. Interestingly, laboratory fear conditioning studies have shown that an imagery intervention to modulate threat imagery enhances extinction learning and reduces return of fear [31–33]. Preliminary research has also shown promising results of clinical interventions that specifically focus on threat imagery in anxiety disorders, such as imagery rescripting [34–37] or EMDR therapy [38–40].

EMDR therapy was developed to alleviate the distress associated with traumatic memories [41]. During EMDR therapy, patients recall a traumatic memory while simultaneously focusing on another task (such as making eye movements by tracking the therapist’s fingers). A large body of experimental research suggests that the emotional intensity and vividness of aversive memories can be reduced when the person performs a distracting task that taxes working memory while recalling the aversive memory [42–44]. Because similar neural mechanisms are involved in past and future memories [45], EMDR therapy may also be effective to modulate fear-related future memories. Pre-clinical laboratory research has indeed shown that an EMDR lab analog modulates future-oriented threat memories [26, 46, 47]. Accordingly, a clinical EMDR “flash-forward” protocol has been developed [48].

Several randomized controlled trials found that EMDR therapy focused on past aversive events reduces anxiety symptoms [39, 40], but the majority have methodological limitations, including the risk of bias, small samples, and the lack of an active control condition [38, 40]. No research so far has tested whether modulation of flashforwards reduces anxiety symptoms in itself and/or enhances efficacy, tolerability, and adherence of exposure-based therapy in patients with anxiety disorder. The primary aim of the present study is to test the efficacy, tolerability, and adherence of this promising approach [23, 49]. To control for nonspecific factors, we will use an active, nonspecific and nondirective intervention aimed at offering support (supportive counseling) [50]. Patients with panic disorder will be the focus of the study, because mental images of threat are prominent in this disorder [21]. Furthermore, panic disorder is prevalent, which enhances the study’s feasibility [51].

## Goals of the current study:

The main goal of this multicenter Randomized Controlled Trial is to investigate whether EMDR therapy with exposure therapy, relative to supportive counseling with exposure therapy, improves treatment efficacy, tolerability, and adherence in patients with panic disorder. The primary outcome measures are panic-related symptoms. Secondary outcome measures are: tolerability of exposure therapy (initial avoidance, willingness to start exposure therapy, considered drop-out; no-show and drop-out), related symptomatology (generalized anxiety, depression) and functional impairment. We hypothesize that: (1) EMDR therapy will be more effective in reducing panic-related symptoms, compared to supportive counselling from baseline (T1) to between-treatments (T2). (2) EMDR therapy + exposure therapy will be more effective in reducing panic-related symptoms, compared to supportive counseling + exposure therapy at post-treatment (T3). (3) EMDR therapy will result in higher tolerability of exposure therapy (less initial avoidance, more willingness to start exposure therapy, less considered drop-out; less no-show and actual drop-out) compared to supportive counseling. We further hypothesize that: (4) EMDR therapy will be more effective in reducing related symptomatology (generalized anxiety, depression) and functional impairment, compared to supportive counseling from baseline (T1) to between-treatments (T2). And (5) EMDR therapy + exposure therapy will be more effective in reducing related symptomatology (generalized anxiety, depression) and personal suffering/functional impairment, compared to supportive counseling + exposure therapy at post-treatment (T3).

Hypotheses concerning the following secondary goals will be preregistered on the Open Science Framework [52]. The first goal is to test whether EMDR therapy + exposure therapy results in less return of fear (panic related symptoms, generalized anxiety), compared to supportive counseling + exposure therapy from posttreatment (T3) to follow up (FU1 and FU2). The second goal is to unravel predictors of optimal treatment allocation (EMDR therapy + exposure therapy > supportive counseling + exposure therapy). These include theory-driven variables (reduced extinction learning, less experienced life events, low intolerance of uncertainty, anxiety sensitivity, low worrying, enhanced imagery ability), patient variables (e.g., greater treatment credibility, better working alliance) and therapist factors (e.g., enhanced trait anxiety, better working alliance, greater treatment expectancy). The third goal is to elucidate mechanisms of change (most notably mental threat imagery, encapsulated threat beliefs) of this novel approach (EMDR therapy + exposure therapy). Finally, we will assess cost-effectiveness of the new approach (EMDR therapy + exposure therapy).

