**Fig. 2 Fig2:**
[figure not shown]
Design flowchart; T1-3: measurements, FU1-2: follow up measurements. EMDR: EMDR therapy, SC: supportive counselling

After baseline measurements (T1), participants will be randomly allocated to one of two conditions: (1) four weekly EMDR therapy sessions followed by eight exposure therapy sessions or (2) four weekly supportive counseling sessions followed by eight exposure therapy sessions. Total study duration is 16 weeks (week 1: baseline measurement T1, week 2: case conceptualization, week 3–6: treatment phase 1; EMDR therapy or supportive counseling, week 7: between-treatments measurement T2, week 8–15: treatment phase 2; exposure therapy, week 16: post-treatment measurement T3). Follow up 1 measurement (FU1) and follow up 2 measurement (FU2) will be conducted one month and six months post-treatment measurement (T3). At FU1, the clinician and participant will determine whether additional treatment is needed. Measurement are conducted by a research assistant blind to treatment allocation. The research protocol has been approved by the Medical Ethical Committee of University Medical Center Utrecht (NL NL73918.041).

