### Randomization

After baseline measures (T1) participants are randomized to one of the two conditions by a research assistant who does not conduct assessments, using computerized randomization (REDCAP) [53, 54]. Stratified randomization will be used to reduce bias by treatment center [55], to guarantee a balanced distribution of participants across conditions.

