#### Instruments goal 2: unravel theory-driven variables (e.g., traits and clinical profiles) and non-specific patient and therapist factors predicting treatment outcome and optimal treatment allocation

Table 2 presents additional measures to examine secondary goals.

**Table 2 Tab2:** Additional measures to test goal 2: unravel theory-driven variables (e.g., traits and clinical profiles) and non-specific patient and therapist factors predicting treatment outcome and optimal treatment allocation

	**T1**	**Tp1**	**T2**	**Tp2**	**T3**	**FU1**	**FU2**

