***Questionnaires for all patients***							
Survey of Autobiographical Memory (SAM) (14)	X	-	-	-	-	-	-
Impact of Event Scale past (15)/future (15)	X	-	X	-	X	X	X
List of Threatening Experiences (LTE) (12)	X	-	-	-	-	-	-
Dutch credibility and expectancy scale (CEQ) (8)		X		X	-	-	-
Working Alliance Inventory-12 (WAI-12) (12)	-		X		X	-	-
Intolerance of Uncertainty Scale (IUS) (12)	X	-	-	-	-	-	-
Anxiety Sensitivity Index (ASI) (18)	X	-	-	-	-	-	-
Penn State Worry Questionnaire (PSWQ) (16)	X	-	-	-	-	-	-

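### Goal 2 names patient credibility and working alliance as predictors of optimal treatment allocation, but Table 2 first measures them after randomisation, so as scheduled they cannot answer the allocation question

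*Protocol article*

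**What the plan says.** Under Goals of the current study, the protocol article states: "The second goal is to unravel predictors of optimal treatment allocation", and adds in brackets that this means the EMDR sequence doing better than the counseling sequence. The variables listed include "patient variables (e.g., greater treatment credibility, better working alliance) and therapist factors"; the examples of therapist factors are trait anxiety, working alliance and treatment expectancy. The heading of the goal 2 instruments section repeats the purpose: "non-specific patient and therapist factors predicting treatment outcome and optimal treatment allocation".

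The Randomization section fixes the order of events: "After baseline measures (T1) participants are randomized to one of the two conditions". Study design and general procedure says the same and places case conceptualization (week 2) and treatment phase 1 (weeks 3 to 6) after T1 (week 1).

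Table 2 gives the measurement times. Tp1 and Tp2 are defined there as the EMDR-or-counseling phase and the exposure phase. Data analysis leaves the analysis strategies for goals 2 to 4 to a pre-registration on the Open Science Framework.

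**The concern.** A variable can help to choose between two treatments only if its value is known before the choice and does not depend on which treatment is then given. A rating first taken after allocation fails the first condition and may fail the second. Alliance with a study therapist forms during treatment. Credibility rated in phase 1 comes after the patient has been allocated to one treatment.

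Two things are at stake. First, a clinician deciding between the sequences would not have these values, so a finding on them could not be used as an allocation rule. Second, a post-randomisation rating can carry information about response or prognosis. If it does so to a different degree in the two arms, a rating-by-arm interaction can arise although the treatment effect is the same for everyone. Read under the goal 2 wording, such an interaction would look like evidence on who should receive EMDR first.

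**Working it through.** **Step 1: timing.** Randomisation falls after T1. The Table 2 entries, over its seven columns from T1 to FU2, are:

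| Measure | Marked at | Before randomisation? |
|---|---|---|
| Patient CEQ | Tp1, Tp2 | No |
| Patient WAI-12 | T2, T3 | No |
| Therapist WAI-12 | Tp1, Tp2 | No |
| Therapist outcome-prediction survey | Tp1 | No |
| SAM, LTE, IUS, ASI, PSWQ | T1 | Yes |
| IES past/future | T1, T2, T3, FU1, FU2 | T1 value only |
| Fear conditioning task | T1, T3 | T1 value only |
| Therapist demographics, ATPTM, EBPAS, CS | T1 | Yes |

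Some cells in the CEQ and WAI-12 rows are blank rather than dashed, but the column count is intact and no T1 mark is present. This step settles the main point and needs no arithmetic. The plan states no figure here to reproduce.

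**Step 2: can false moderation arise?** The plan gives no feedback sizes, so every parameter below is an assumption. The sample is 25 per arm, from the planned 50. The model is:

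- improvement = 0.5 × arm + N(0,1), so the treatment effect is constant and there is no moderation;
- alliance = N(0,1) + b × improvement, with b set separately in each arm, then standardised;
- least-squares regression of outcome on arm, alliance and arm × alliance, with the interaction tested two-sided at 5%.

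In the column for the same visit, the outcome is the improvement that feeds alliance (WAI-12 at T2 with the T2 outcome, or T3 with T3). In the last column, T2 alliance predicts a T3 outcome whose correlation with T2 improvement is taken as 0.5. Results from 10,000 runs per cell:

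| b EMDR / b counseling | Mean false interaction, same visit | False positives, same visit | False positives, T2 alliance to T3 outcome |
|---|---|---|---|
| 0.5 / 0.5 | 0.00 | 5% | 5% |
| 0.5 / 0.4 | 0.06 | 5% | 5% |
| 0.5 / 0.2 | 0.22 | 12% | 7% |
| 0.8 / 0.2 | 0.35 | 25% | 9% |
| 0.5 / 0 | 0.42 | 31% | 11% |

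**Step 3: a second mechanism.** Here the rating reflects an unmeasured baseline prognosis instead of improvement. Prognosis affects the outcome with weight 0.7, the rating is shifted by 0.5 SD in the EMDR arm, and the treatment effect is a constant 0.50 SD. At a total of 50, the interaction is falsely significant in 4.5% of runs when the rating correlates 0.5 with prognosis in both arms. The rate is 16% at 0.6/0.2, 31% at 0.7/0.1 and 42% at 0.7/0. The arm coefficient in the same model falls from the true 0.50 to between 0.25 and 0.33, even in the equal case (0.33). A variable fixed before randomisation keeps the interaction test at about 5% in all of these scenarios.

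**The case against.** **The analysis is not yet specified.** Goals 2 to 4 are left to a pre-registration, and no credibility-by-arm or alliance-by-arm model is written in the article. That is true, and the missing model is not the complaint. The named predictors and the schedule are both stated, and a later analysis plan cannot supply a baseline value that was never collected.

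**Other uses are legitimate.** The instrument headings speak of predictors, mediators and moderators, and goal 2 covers treatment outcome as well as allocation. Post-randomisation alliance and credibility are proper outcome predictors or candidate mediators. This stands, and the fix keeps those uses. Only the allocation role fails.

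**Not every rating looks back.** The CEQ includes expected improvement, and the therapist survey asks for a prediction and for suitability. The article does not say when within Tp1 they are given, so the first could precede any phase 1 session. This stands too: the feedback calculation concerns alliance and does not establish that phase 1 improvement raises the first CEQ. Both measures are still taken after allocation.

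**The larger rates are extreme cases.** About 30% in the feedback model requires alliance and outcome at the same visit and no feedback at all in the counseling arm. The counseling protocol was designed to match therapeutic alliance, and the documents give no evidence of such a difference between arms. With nearly equal feedback the test stays close to 5%.

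**Stronger readings.** A reader might infer that goal 2 will produce false moderators, or that the trial's main result is compromised. The documents support neither. False moderation depends on an arm difference that nobody has measured, and goal 2 is secondary. A reader might also connect this with therapist trait anxiety, which goal 2 names although the article describes no instrument for it. That is an example item in a condensed listing, and it has no bearing on the timing problem.

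**Conclusion.** The point holds. Patient credibility and patient and therapist working alliance are named as predictors of optimal allocation but are first measured after randomisation, so as scheduled they cannot answer that question. This follows from the text and Table 2 alone and rests on no assumption.

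The risk of false moderation is possible but not demonstrated. In the feedback model its size runs from the nominal 5% under equal feedback to about 30% under one-arm feedback at the same visit. With T2 alliance predicting T3 outcome the highest rate was 11%. The prognosis model spans 4.5% to 42%, the top figure needing a correlation of 0.7 in one arm and none in the other. All of these feedback and correlation sizes are assumed.

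The matter should be corrected before the goal 2 analyses are fixed. It does not touch the primary comparison.

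**What to change.** In goal 2 and in its pre-registration, state that the optimal-allocation (moderator) analysis uses only variables measured at T1 before randomisation. These are SAM, IES/IFES, LTE, IUS, ASI, PSWQ, the T1 fear conditioning task and the therapist T1 scales. State that CEQ and WAI-12 enter only as process variables, outcome predictors or candidate mediators, and treat the therapist outcome-prediction survey at Tp1 as post-randomisation as well.

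This changes wording only. It needs no new data and no change to visits, and recruitment is still open with the pre-registration described as yet to come. The cost is that credibility and alliance are dropped as allocation predictors. Having patients rate both treatments at T1 would be a separate design decision: it could bring in preference or disappointment effects, and patients already enrolled would lack the measure. It is not needed to correct this point.

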## Methods/design

### Study design and general procedure

A multicenter, single blind, randomized controlled trial with a two-arm mixed factorial design is used with two groups (EMDR therapy + exposure therapy, supportive counseling + exposure therapy) and three time points (T1: baseline; T2: between-treatments and; T3: posttreatment). The design is presented in Fig. 1 and a flowchart is presented in Fig. 2.

**Fig. 1 Fig1:**
[figure not shown]
Study design; T1-3: measurements, S1-4/8: sessions, FU1-2: follow up measurements. EMDR: EMDR therapy, SC: supportive counselling, ET: exposure therapy

**Fig. 2 Fig2:**
[figure not shown]
Design flowchart; T1-3: measurements, FU1-2: follow up measurements. EMDR: EMDR therapy, SC: supportive counselling

After baseline measurements (T1), participants will be randomly allocated to one of two conditions: (1) four weekly EMDR therapy sessions followed by eight exposure therapy sessions or (2) four weekly supportive counseling sessions followed by eight exposure therapy sessions. Total study duration is 16 weeks (week 1: baseline measurement T1, week 2: case conceptualization, week 3–6: treatment phase 1; EMDR therapy or supportive counseling, week 7: between-treatments measurement T2, week 8–15: treatment phase 2; exposure therapy, week 16: post-treatment measurement T3). Follow up 1 measurement (FU1) and follow up 2 measurement (FU2) will be conducted one month and six months post-treatment measurement (T3). At FU1, the clinician and participant will determine whether additional treatment is needed. Measurement are conducted by a research assistant blind to treatment allocation. The research protocol has been approved by the Medical Ethical Committee of University Medical Center Utrecht (NL NL73918.041).

